| Pulse checks at correct times                                             | Pulse checks according to ERC ALS guidelines                                                                                                                                                                                    |
| Continuous ventilation while chest compressions in correct rate (10/min)  | Order/feedback from the team leader to the team member at the airway. If this feedback is not given, the team member is instructed to ventilate too quickly (approximately 15-20/min)                                           |
| FiO 2 set to 1.0                                               | Order/check                                                                                                                                                                                                                     |
| Recognition of tension pneumothorax as reversible cause of cardiac arrest | Must be pronounced aloud; or by obvious initiation of mini-thoracotomy after POCUS or clinical observation (ventilatory effort, auscultation, etc.)                                                                             |
| Mini-thoracotomy                                                          | Order or initiation by the team leader                                                                                                                                                                                          |
| Medications                                                               | Medications, time intervals and dosage according to ERC ALS guidelines                                                                                                                                                          |

|                                     |                                                                                                  |
|-------------------------------------|--------------------------------------------------------------------------------------------------|
| Arterial blood gas                  | Order or initiation by the team leader (if not already done in the primary/secondary assessment) |
| Check of possible reversible causes | Check according to ERC guidelines                                                                |

*CPR = cardiopulmonary resuscitation, eFAST = extended focused assessment with sonography for trauma, POCUS = point-of-care ultrasound*

Table 2 provides a comprehensive list of items that are deemed protocol deviations until the necessary action is explicitly carried out or verbally communicated in its entirety. For an action or order to be considered timely in this context, it must be completed within the corresponding chronological category outlined in Table 2, which includes Primary Assessment → Secondary Assessment → Advanced Life Support. It is important to note that these determinations are made by an expert in the field, relying on their professional judgment. Each protocol deviation can only be committed once. Actions ordered or performed by the team leader are considered equivalent in this regard.

It should also be noted that all orders and actions can be successfully completed on the first attempt to further standardize the scenario in the setting of this study.

After each scenario, a standardized full-team debriefing will be conducted, focusing on critical actions and protocol deviations. Questionnaire 2 will also need to be filled in by each participant at this point in the study.

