## 3.2 Study design

This study is a single-center, prospective, single-blind, randomized, controlled trial. It aims to assess the efficacy of VR as a more effective preparation method for in-person simulation trainings, compared to e-learning. The focus is on improving physicians' trauma CPR management skills.

All recruited participants will watch a 60-minute video to learn about the requirements, steps, and other important information about this study. Furthermore, this introductory video will give an overview of management strategies for trauma patients going into cardiac arrest in an in-hospital setting and provides links to the guidelines (30–32) on which this study is based. It also indicates that knowledge of the content of the guidelines is a prerequisite for Phases 2 through 3. This video can be viewed as often as desired throughout the study. Participants will also be required to complete the electronic Questionnaire 1 (Additional file #2) prior to randomization, which assesses participants' baseline characteristics (including the German versions of the "Openness to Experience" subscale of the 100-item HEXACO-PI-R test (33,34) and the Technology Readiness Scale (35)).

Each participant will then complete either the e-learning course (control group) or the VR training simulations (intervention group) over a two-week period, both focusing on the same content. Both groups will spend approximately the same amount of time learning the same content, which will prepare the participants for the assessment in the simulation session. If participants do not complete the entire e-learning course or all four VR simulations, they will be dropped from the study.

After Phase 2, all participants will attend the simulation session and will be evaluated in the role of medical team leader of a standardized TCA scenario (Phase 3).

In addition, each participant will be required to complete Questionnaire 2 (Additional file #3) immediately following the simulation session in Phase 3. Only the intervention group will be required to complete the VR system usability portion of this questionnaire. The system usability scale (SUS) (36,37) will be translated and used in German.

[figure not shown]

**Figure 1.** The course of events during the study.

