#### **Cognitive load:**

Cognitive load will be assessed immediately after the simulation scenarios using the NASA TLX questionnaire, included in Questionnaire 2, the gold standard for measuring subjective workload. The workload score is based on a weighted average of ratings on six sub-dimensions, including mental demand, physical demand, temporal demand, performance, effort, and frustration. All six sub-dimensions (ranging from 1 to 100) are included in the questionnaire. In addition, the global Task Load Index (ranging from 1 to 100), which is defined as the arithmetic mean of all subscales, will be calculated.

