| Learning method (participants' impression)                                     |                 |                      |
| - Learning progress                                                            |                 |                      |

|                                                           |                  |                      |
|-----------------------------------------------------------|------------------|----------------------|
| - Level of frustration                                    | Questionnaire 2  | 5-point Likert scale |
| - Level of enjoyment                                      |                  |                      |
| Participants' confidence in management of TCA             | Questionnaires 2 | 5-point Likert scale |
| Participants' performance                                 |                  |                      |
| - Participants' subjective impression                     | Questionnaires 2 | 5-point Likert scale |
| - Experts' impression                                     | Scoring sheet    | 5-point Likert scale |
| VR-related adverse events                                 | Questionnaire 2  | Incidence rate       |
| SUS                                                       | Questionnaire 2  |                      |
| - SUS score                                               |                  | 1 to 100             |
| - Adjective rating scale                                  |                  | 7-point Likert scale |
| Drop-out variables                                 |                  |                      |
| Training/studying with other non-study learning resources | Questionnaire 2  | Yes/no               |
| Insufficient preparation with assigned learning method    |                  | Yes/no               |

---

*ALS = advanced life support; AOI = area of interest; ATLS = advanced trauma life support; CPR = cardiopulmonary resuscitation; ERC = European Resuscitation Council; ETC = European Trauma Course; NASA-TLX = National Aeronautics and Space Administration Task Load Index; PHTLS = prehospital trauma life support; SUS = system usability scale; TCA = traumatic cardiac arrest; VR = virtual reality*

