### **Secondary objectives/outcomes:**

A two-sided generalized Wilcoxon test will also be used to compare times to critical actions, excluding the primary outcome. The number of participants who did not recognize and treat the underlying condition of the TCA, and the number of participants declaring the patient dead prematurely, will be compared between groups calculating the chi-square test. Protocol deviations will be analyzed separately for each protocol deviation listed in Table 2. The respective frequencies of each protocol deviation will also be compared between groups calculating the chi-square test. Fisher's exact test will be used if one or more expected cell frequencies are less than 5.

In addition, the Wilcoxon rank sum test will also be used to compare the gaze behavior (dwell-time in AOIs, fixation count and average fixation duration, and relative time when no AOI is illustrated) and the NASA-TLX scores (global and per objective) between randomized groups.

Furthermore, a multivariable Cox regression model (including an interaction term) will be used to determine the influence of gender on the primary outcome, and the potential modifying effect of gender on the training effect (= group effect). The HEXACO subscale and the Technology Readiness Score will also be included in the multivariable model to adjust for potential imbalances between the randomized groups.

The following Spearman correlation coefficients will be calculated corresponding to the remaining secondary objectives:

- Correlation of 5-point Likert scales between the frequency of playing classic video games and the primary outcome

5-point Likert scales, the incidence rate of VR-related AEs, and the SUS scores will be reported using descriptive statistics only.

Observations with missing data in the primary outcome measure will be excluded from statistical analyses. Boxplots will be used to illustrate calculations. A two-sided p-value of  $< 0,05$  will be considered statistically significant.

Due to the singular primary objective, no correction for multiple testing will be made. All secondary objectives are exploratory in nature and will be used to generate further hypotheses.

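### The order of Questionnaire 2 and the debriefing is not fixed, so workload, confidence and self-rated performance may be collected after feedback

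*Protocol*

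**What the plan says.** Three places in the protocol set the time of Questionnaire 2 or of something inside it.

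- Section 3.2.3 (Simulation sessions) says: "After each scenario, a standardized full-team debriefing will be conducted, focusing on critical actions and protocol deviations". The next sentence says: "Questionnaire 2 will also need to be filled in by each participant at this point in the study".
- Section 3.2 (Study design) requires each participant to "complete Questionnaire 2 (Additional file #3) immediately following the simulation session in Phase 3".
- Section 3.2.4 (Performance assessment), in the paragraph on cognitive load, says: "Cognitive load will be assessed immediately after the simulation scenarios using the NASA TLX questionnaire, included in Questionnaire 2".

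Table 3 in Section 3.4.1 shows what depends on this form. It is the source for the NASA-TLX, for "Participants' confidence in management of TCA" and, under participants' performance, for "Participants' subjective impression". Section 3.5 compares "the NASA-TLX scores (global and per objective) between randomized groups" with a Wilcoxon rank sum test. It limits the 5-point Likert items to descriptive statistics and calls all secondary objectives exploratory.

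**The concern.** Secondary objective 6 in Section 2.3 concerns the load felt while leading the scenario. Objectives 8d and 8e concern the participant's own confidence and own view of performance in the simulation. Each is useful only as a report of the experience itself. The debriefing deals with the same critical actions and deviations on which the participant's performance is judged. Someone who answers after that discussion may be reporting, in part, what was said there. The NASA-TLX subscales for performance and frustration, and the self-rating, look most open to this.

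The debriefing format is the same in both arms, but the discussion can be expected to follow what happened in each scenario. If the arms perform differently, as the trial hypothesizes, the feedback will differ too, and some of that difference could enter the self-reports. If some sessions hand out the form before the debriefing and others after it, the answers are also no longer taken under one condition. The order of collection cannot be repaired in the analysis.

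**Working it through.** No figure in the protocol bears on the order of these steps, so the check is a comparison of the passages.

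1. **Which events need an order?** There are three: the end of the scenario, the debriefing and Questionnaire 2. The assessment ends at 15 minutes. If the cause was not treated, a specialist takes over and the scenario runs 3 minutes more, to 15 + 3 = 18 minutes.

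2. **What does Section 3.2.3 fix?** Both the debriefing and the questionnaire come after the scenario. The debriefing is named first. The link between the two sentences is a phrase about the point reached in the study, which can mean after the scenario or after the debriefing just described. The order between the two is open.

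3. **What does Section 3.2 fix?** The form follows the simulation session: "immediately following the simulation session in Phase 3". The extent of the session is not defined. The debriefing is described within the section titled Simulation sessions, which suggests that the session may include it. The opening of that section equates the sessions with the assessments, and these end at 15 minutes, which suggests that it may not.

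4. **What does Section 3.2.4 fix?** The NASA-TLX comes immediately after the scenario. Taken at its word, this leaves no room for a debriefing in between. It is written for cognitive load only and does not mention confidence or self-rated performance.

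5. **Do the possible orders fit?**
   - Scenario, questionnaire, debriefing: fits all three places.
   - Scenario, debriefing, questionnaire: fits Section 3.2.3 as written and Section 3.2 if the session includes the debriefing. It does not fit Section 3.2.4.

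   One order satisfies everything, but no sentence states it. Staff who work from Section 3.2.3 in written order would follow the other.

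6. **Which outcomes are exposed?** There are six NASA-TLX subscales plus the global index, 6 + 1 = 7 scores, all tested between arms. Two Likert items on the scenario itself, confidence (8d) and self-rated performance (8e), are reported descriptively.

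7. **Which are not?** The primary outcome, the times to the other critical actions, the protocol deviations and the expert rating come from the scoring sheet, completed from video by blinded experts. Gaze measures are recorded during the scenario. The position of the questionnaire affects none of these.

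**The case against.** The strongest reply is that the protocol has already settled the matter. Section 3.2.4 gives the time of the NASA-TLX, the NASA-TLX sits inside Questionnaire 2, and completing the form before the debriefing satisfies every passage. On that view Section 3.2.3 merely lists two things that happen after the scenario. This stands to a large extent. A reader might infer that the protocol orders the questionnaire after the debriefing, or that its sections flatly contradict each other. The text supports neither reading. What remains is that the intended order has to be pieced together from another section, while the operational section suggests a different one.

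Other points also carry weight:

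- Figure 1, on the course of events, and Questionnaire 2 itself were not available for this review. Either might state the order.
- Participants who do not treat the cause see a specialist take over at 15 minutes. They know of the failure before any questionnaire, so moving the form does not make their answers free of feedback. The debriefing still adds detail, and it reaches every participant.
- The debriefing is standardized and applied in both arms. Formal scoring follows later, in Phase 4, so the debriefing cannot pass on scoring-sheet results. It does cover the same actions.
- The ratings of learning progress, frustration and enjoyment (8a to 8c) refer to the two-week preparation, not to the scenario. An effect of the debriefing on them would be conjecture, and they are not counted here.
- The trial is single-center, so the order cannot differ between sites. It could differ only between sessions or staff.

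**Conclusion.** The point holds as an unfixed order of data collection. The written sequence allows the questionnaire to follow the debriefing. Seven tested NASA-TLX scores and two descriptive items may then partly reflect feedback.

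The reach is limited. All the affected outcomes are exploratory, and the primary and other video-scored outcomes are untouched. A reader might infer a bias for or against the VR arm. The documents do not support that: they give no direction and no figure from which a size could be derived.

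The conclusion rests on two assumptions: that neither Figure 1 nor the questionnaire form states the order, and that the debriefing touches on the participant's own actions, as its stated focus implies. If the figure or the form does state the order, only an alignment of the text is left to do. The change is still worth making, because it protects a planned comparison between arms, cannot be made once the data are collected, and costs almost nothing.

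**What to change.** Align Sections 3.2, 3.2.3 and 3.2.4 to one sequence: the scenario ends (at 15 minutes, or after the additional 3 minutes if the specialist has taken over), each participant completes Questionnaire 2 and hands it in, and only then does the debriefing start.

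A suitable sentence for Section 3.2.3 is: Each participant completes Questionnaire 2 after the scenario has ended and before any debriefing or feedback is given. Section 3.2 should then name the end of the scenario, rather than the session, as the reference point.

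If the whole form is too long to complete at that moment, the NASA-TLX, confidence and self-rated performance items should at least be taken before the debriefing.

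The cost is a small text change in three places and a debriefing that begins a few minutes later. Sample size, staffing, analysis and the content of the debriefing stay as they are.

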### 3.2.4 Performance assessment

The video recordings, as described in Section 3.2.3, will be analyzed in Phase 4 by blinded experts. The experts will not be involved in the conduct of the study and therefore do not know which group an individual was randomly assigned to in Phase 2. For this reason, the videos presented to the experts are labeled only with an assigned participant ID. To avoid inter-rater variability in the assessments, experts will be given two easy-to-score and two hard-to-score exercise cases to evaluate independently in advance. The results are then discussed among the experts and with the study team to resolve any ambiguities or disagreements and to reach a consensus on further evaluation.

The video recordings themselves will be edited in such a way that the expert is presented with only one compact video of each scenario/assessment, which includes the simultaneous recordings from the cameras pre-installed in the simulation room and the video recording from the participant's perspective through the eye-tracking glasses. These recordings can be viewed and rewound as many times as needed in their final edited form.

In the ALS courses of the ERC, the strategy of mastery learning and mastery testing of skills is used in the context of ALS scenario training and assessment (42), i.e. key objectives are defined that are of particular importance and to which special attention is paid in the assessment. In line with this, a similar focus is also taken in this study. Therefore, the primary outcome measure is the time taken to the most critical action (Table 1; critical action #3), as described in Section 3.2.3. This time (in minutes and

seconds) will be assessed by reviewing the video recordings. The times to the completion of the other critical actions (Table 1; critical actions #1 and #2) will also be measured as secondary outcomes.

If participants do not recognize the underlying condition of the TCA and therefore do not complete all of the critical actions listed in Table 1 within 15 minutes, and therefore only with the assistance of the additional specialist, these times will be considered censored observations (at 15 minutes). The number of such cases will be reported as a secondary outcome.

If patients are declared dead prematurely (before the 15-minute time limit), the time to completion of the respective critical action will also be censored at 15 minutes, and the number of such cases will be reported.

The protocol deviations listed in Table 2 will also be assessed from the video recordings. In this context, untimely is defined as not performed within the following chronological categories:

1. Primary assessment (x – A – B – C – D – E)
2. Secondary assessment
3. ALS according to the ERC's sequence for TCA

The simulated scenario will end at exactly 15 minutes with ROSC achieved if all critical actions have been completed before the allotted time has elapsed. For a positive learning outcome and scenario completion, if the underlying cause is not identified and treated, a simulated specialist in anesthesiology and intensive care will intervene in the scenario at exactly 15 minutes and will provide critical assistance to allow the scenario to still result in ROSC after further 3 minutes. The assessment will end at 15 minutes, regardless of the possible situations described.

All variables collected in Phase 4 will be documented by the experts in the scoring sheet (Additional file #4).

#### **Cognitive load:**

Cognitive load will be assessed immediately after the simulation scenarios using the NASA TLX questionnaire, included in Questionnaire 2, the gold standard for measuring subjective workload. The workload score is based on a weighted average of ratings on six sub-dimensions, including mental demand, physical demand, temporal demand, performance, effort, and frustration. All six sub-dimensions (ranging from 1 to 100) are included in the questionnaire. In addition, the global Task Load Index (ranging from 1 to 100), which is defined as the arithmetic mean of all subscales, will be calculated.

#### **Eye-Tracking:**

Differences in gaze behavior between the randomized groups in Phase 3 will be assessed in terms of dwell time on different AOIs, number of fixations, and average fixation duration. Defined AOIs are the manikin's head/airway, the manikin's thorax, the vital signs monitor, and the ventilator monitor. The

number of fixations is defined as the number of times participants fixate different AOIs, and the average fixation duration is the average time for fixations within an AOI. The greater the average fixation duration, the greater the level of cognitive engagement.

Furthermore, the relative time when no AOI is illustrated will be analyzed.

